#### Secondary Outcome Measures

The secondary outcomes were unmet informational needs, quality of life, distress, and symptoms. Unmet informational needs were assessed using the information needs scale (3 items) from the Korean version of the Cancer Survivors’ Unmet Needs scale [26,27]. Health-related quality of life is measured using the Korean version of the European Organisation for Research and Treatment of Cancer Quality of Life Questionnaire—Core 30 [28]. Distress was assessed using the National Comprehensive Cancer Network Guidelines for Distress Management (version 2.2021) [29]. The European Organisation for Research and Treatment of Cancer Quality of Life Questionnaire—Lung Cancer 13 [30], the Chronic Obstructive Pulmonary Disease Assessment Test [31,32], and the modified Medical Research Council dyspnea scale [33] are used to assess the presence and severity of symptoms related to lung cancer.

The Korean version of the International Physical Activity Questionnaire-Short Form is used to identify participants’ levels of physical activity [34]. Depending on the level of activity derived from the questionnaire, patients were categorized into high, moderate, or low groups. The Hospital Anxiety and Depression Scale is a measure of depressive mood [35]. The components of each intervention and the hypothesized effects on the primary and secondary outcomes are shown in Figure S3 in Multimedia Appendix 1.

Sociodemographic variables such as age, sex, and level of education were acquired directly from the participants via self-reported questionnaires. Clinical characteristics, such as cancer stage, type of treatment, and postsurgical complications, were obtained from electronic medical records.

### Sample Size Calculation

Based on the primary hypothesis that the intervention group would demonstrate a 25% better psychological adjustment to cancer at 6 months after surgery than the control group, initial calculations with an effect size of 0.25 indicated that 252 participants per group would be required. We aimed for a sample size of approximately 300 per group to account for a dropout rate of 16%. However, to increase the robustness of our findings, allow for potential subgroup analyses, and ensure that the study had sufficient power to detect smaller effect sizes, we enrolled 400 participants per group. The sample size significantly exceeded the required number based on our initial estimates, thereby enhancing the statistical power and potential impact on the study's outcomes.

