### Statistical Analysis

To assess the effectiveness of LC^3^P, we compared the outcomes between the intervention and control groups at multiple time points. The primary analyses involved independent sample 2-tailed *t* tests for continuous variables and chi-square tests for categorical variables to compare baseline characteristics and outcomes between the 2 groups at each follow-up. To account for repeated measures within participants over time and potential within-subject correlations, a mixed-model repeated-measures analysis was used.

In addition to primary analyses, sensitivity analyses probed the robustness of the trial findings under different assumptions regarding missing data and the effects of protocol adherence on treatment outcomes. This included intention-to-treat and per-protocol analyses. Moreover, subgroup analyses were conducted to examine the variability in treatment effects across different patient characteristics such as age, cancer stage, and the presence of comorbid conditions. All tests were 2-tailed, with a significance level of *P*<.05. To address multiple testing concerns, particularly with numerous secondary outcomes, we used Bonferroni correction or other suitable adjustments to preserve the overall type I error rate. All statistical analyses were conducted using STATA/MP (version 16.0; StataCorp).

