## Results

The historical control group (n=441) was recruited from September 8, 2021, to April 20, 2022, and the intervention group (n=350) was recruited from April 22, 2022, to October 17, 2022. All statistical analyses will be performed upon completion of the study.

As part of a nationally funded study, the results and details of the procedures will be made publicly available upon completion. The findings of this study will be actively shared through publications in peer-reviewed academic journals and at national and international scientific conferences. Regarding the intervention, the content and access to the educational videos will be refined based on the feedback patients provide on their first follow-up visit and will be made available on YouTube and to other health care professionals within the same health care institution, including oncologists and oncology nurses. The full protocol for this study is currently available at the ClinicalTrials.gov (NCT05078918). The raw data for this study will be shared upon request.

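### The sample size section reports 400 enrolled per group, but the article's own counts are 441 and 350; the figure is wrong, though the effect on overall power is negligible

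*Protocol article*

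**What the plan says.** The Sample Size Calculation section moves through three figures. It begins with the requirement: "initial calculations with an effect size of 0.25 indicated that 252 participants per group would be required". It raises this to about 300 per group for 16% dropout, and presents that figure as an aim. It then says, in the past tense and without qualification, that "we enrolled 400 participants per group". The reasons given for the increase are robustness, room for possible subgroup analyses, and the wish to "ensure that the study had sufficient power to detect smaller effect sizes". The section closes by saying that the size is well above the requirement and so raises power. It gives no power, standard error or detectable effect for 400 per group.

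The Results section gives different counts. On the controls it reads: "The historical control group (n=441) was recruited from September 8, 2021, to April 20, 2022". The count it gives for the other arm is also not 400: "the intervention group (n=350) was recruited from April 22, 2022, to October 17, 2022". The Abstract repeats both. Neither place mentions 400 or explains why the groups differ in size.

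**The concern.** One article gives two incompatible accounts of how many people entered the trial. The section that states the trial's size is the one with the wrong figure. A reader who takes the sample size from there will believe in a balanced design of 800. Someone who later compares the protocol with the results paper will find 50 intervention participants unaccounted for and an imbalance that was never explained. The comparison is non-randomised and uses a historical control group, so accurate counts per group are basic information.

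The figure also sits directly beneath the section's statements about power. It is reasonable to ask whether those statements survive when the actual counts are used.

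**Working it through.** **Can the counts be reconciled?**

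| | Sample Size Calculation | Abstract and Results | Difference |
|---|---|---|---|
| Control | 400 | 441 | +41 (+10.3%) |
| Intervention | 400 | 350 | −50 (−12.5%) |
| Total | 800 | 791 | −9 (−1.1%) |

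- Exclusions after enrolment: Eligibility Criteria allows for cancelled resection, confirmed stage IV disease and withdrawal. These could bring 441 down towards 400, but they cannot bring 350 up to 400.
- Timing: intervention recruitment closed on October 17, 2022 and the article appeared in February 2024, so 350 is not an interim count.
- Approximation: the 300 is described as approximate and as an aim. The 400 is described as neither.

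No reading makes both statements true.

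**Reproducing the plan's own figures.** Inputs: effect size 0.25, taken as a standardised mean difference (SD = 1); two-sided alpha 0.05, from Statistical Analysis; power not stated, so 80% is tried first.

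- n per group = 2 × (1.960 + 0.842)² / 0.25² = 2 × 2.8016² / 0.0625 = 251.2, which rounds up to 252. This matches.
- Alternatives do not match: 90% power gives 337 and a one-sided test gives 198. Two-sided 80% is therefore the inferred basis.
- Dropout: 252 / (1 − 0.16) = 300. This matches.
- The 400 follows from no formula in the article.

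**Effect of the wrong count.** The relevant comparison is 441/350 against 400/400.

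Formulas, in SD units: SE = √(1/n₁ + 1/n₂); effect detectable at 80% power = 2.8016 × SE; power at d = Φ(d/SE − 1.960).

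After 16% dropout, 441 × 0.84 = 370.4 and 350 × 0.84 = 294, while 400 × 0.84 = 336.

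| | 400/400 | 441/350 |
|---|---|---|
| SE, no dropout | 0.0707 | 0.0716 |
| Power at 0.25, no dropout | 94.2% | 93.7% |
| Detectable effect, no dropout | 0.198 | 0.201 |
| SE, 16% dropout | 0.0772 | 0.0781 |
| Power at 0.25, 16% dropout | 90.0% | 89.3% |
| Power at 0.20, 16% dropout | 73.6% | 72.6% |
| Detectable effect, 16% dropout | 0.216 | 0.219 |

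The SE ratio is 0.07159 / 0.07071 = 1.012. The balanced design equivalent to 441/350 has 2 × 441 × 350 / 791 = 390 per group.

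**Sensitivity to dropout at 441/350.** Power at 0.25 is 91.2% at 10% dropout, 87.8% at 20%, and 84.2% at 28%, where the intervention group reaches 350 × 0.72 = 252.

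**The case against.** The strongest reply is that this is a slip of wording with no consequence. The correct counts appear twice in the same article, so no reader is deprived of them. No numerical precision is claimed for 400 per group. The qualitative claims hold at the actual counts: both groups exceed 300, both exceed 252 after the planned dropout, and the effect detectable at 80% power is below 0.25 SD. On consequence, this reply is right. It does not rescue the sentence itself, which states a current fact that the Results section contradicts.

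Two stronger readings are tempting, and the document supports neither.

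- A reader might infer that the power claim rests on the wrong count and falls with it. It does not, because 441/350 supports the same claim almost as well as 400/400. The 12.5% shortfall in one group, taken alone, ignores the 41 extra controls.
- A reader might infer that the miscount undermines the subgroup analyses. For an even two-way split, the interaction detectable at 80% power is 2 × 0.219 = 0.44 SD at the actual counts and 2 × 0.216 = 0.43 SD at 400 per group, so the limit does not come from the miscount. The section says only that the size leaves room for possible subgroup analyses. It does not say that the trial is powered for subgroup effects.

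**Conclusion.** The point holds as a factual error in the stated sample size: 400 per group is contradicted by 441 and 350, and the documents offer no reconciliation. It does not hold as a loss of precision. Against 400/400, the standard error is about 1% larger and power at 0.25 SD falls by less than one percentage point (90.0% to 89.3% after dropout).

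The contradiction rests on no assumption. The power figures rest on three: that 0.25 is a standardised difference (the section sets it beside a 25% improvement and does not give its units), that planned power was 80%, and that dropout is 16% in both groups. The 1% change in standard error needs only a common SD and equal dropout in the two groups. All figures are for the unadjusted comparison of the two whole groups; adjustment for the historical control would lower precision under either set of counts.

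**What to change.** In Sample Size Calculation, replace the 400-per-group statement with the actual enrolment of 441 controls and 350 intervention participants. The sponsor should confirm whether 400 was a target, since the article never calls it one, and add a sentence on why the groups are unequal.

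Any power statement should use the actual numbers and give its assumptions: for example, about 89% power at 0.25 SD and 80% power at about 0.22 SD, with two-sided 5% alpha and 16% dropout in both groups.

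The cost is a few sentences. No participants are added and no analysis changes.

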### Recruitment

Patients scheduled for pulmonary resection were recruited as controls to prevent contamination. The recruitment and study period for the control group were completed before the start of the intervention to ensure no overlap. Subsequently, recruitment to the intervention group began.

### Data Collection

The clinical trial procedure and intervention are outlined in Figure 1, with the outcomes assessed at baseline (T0), 1 month (T1), 6 months (T2), and 1 year (T3) postoperatively. Baseline data will be collected before surgery and immediately after enrollment. To enhance participant retention and adherence, individuals in both groups received a small token of appreciation upon completion of each of the 3 postoperative follow-up assessments (T1-T3). For participants who discontinued or deviated from the intervention protocols, the data collected up to the point of departure were included in the intention-to-treat analysis to maintain the robustness of the trial results and minimize the impact of attrition bias. The data obtained from self-administered questionnaires were coded and stored in password-encrypted Microsoft Excel (Microsoft Corp) files on a secure computer server. The specific variables measured at each time point are listed in Figure 2.

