#### Delivery of the Intervention

Eligible participants received a brochure containing QR codes linked to educational videos (Figure S2 in Multimedia Appendix 1). We added QR codes for all the videos in a brochure and gave it to participants before surgery so they could preview the videos if they were curious about what to expect and what to work on after surgery. Participants were strongly encouraged to view the first video before surgery. The link to the first video was sent via SMS text message at the time of enrollment to increase patient accessibility. Around the time of discharge, a research assistant visited the intervention group participants to offer them a second copy of the brochure and sent links to each of the 3 videos, reminding them to watch the videos at their convenience. Data on compliance, satisfaction, and feedback on the educational videos were collected during follow-up visits. Measures were taken until the survivors reported watching all 4 videos or at their 1-year follow-up visit.

During the first follow-up visit after discharge, participants in the intervention group were scheduled to visit a family medicine doctor in addition to regular oncology appointments. During their appointment, the participants discussed any physical or psychological difficulties they had experienced after surgery, and the family medicine doctor provided tailored assistance based on the type and depth of their needs. As our intervention was educational, the participants in the intervention group were qualified to receive other concomitant care or additional necessary measures during the study. A flowchart of the study procedure and intervention is shown in Figure 1.

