#### Control Group

Participants in the control group received routine preoperative and discharge information regarding hospital stay, costs, and postoperative care. They did not have access to educational programs or postoperative educational support.

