### Limitations

Despite these advantages, this study has some limitations that must be addressed. First, the design of the intervention might be more appealing to participants who are actively seeking ways to adapt to life after cancer, as opposed to those who are less motivated or indifferent about making such adjustments. In addition, although the use of a historical comparison group was intended to minimize the impact of exposure to our intervention in patients with lung cancer, the limitations of using a nonparallel comparison group should not be ignored. Second, socioeconomic and geographic disparities among older patients with cancer could affect accessibility to web-based educational videos. Although disseminating educational videos through web-based platforms allows cancer survivors to access as much information as they need at their convenience, it can be difficult for survivors with limited access to technology to access this information. If found to be promising, future studies should address the disparities in accessing web-based educational videos. Finally, the trial was registered after the recruitment commenced. However, there were no changes in the study design, measurement, or analysis methods after receiving the initial ethics approval.

In conclusion, the LC^3^P represents a proactive, holistic prehabilitation intervention aimed at supporting lung cancer survivors, as they navigate the transition to life after treatment. Our findings highlight the impact of early informational support on patients’ psychological adaptation and postdiagnosis stress management. This could potentially establish a new standard for the timing and delivery of survivorship care, emphasizing the benefits of early intervention.

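### The intention-to-treat data rule stops at departure from the intervention, which is not intention-to-treat and may remove 6-month scores from the intervention arm alone

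*Protocol article*

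**What the plan says.** The protocol article's only rule on outcome data from non-adherers is in Data Collection: "For participants who discontinued or deviated from the intervention protocols, the data collected up to the point of departure were included" in the analysis called intention-to-treat. The stated aim is "to maintain the robustness of the trial results and minimize the impact of attrition bias". The point of departure is not defined, and nothing is said about scores obtained after it.

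Four other sections bear on the rule:

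- **Control Group.** "Participants in the control group received routine preoperative and discharge information", and "They did not have access to educational programs or postoperative educational support".
- **Delivery of the Intervention.** A research assistant sends the video links around discharge, "reminding them to watch the videos at their convenience". The family medicine visit is set for the first follow-up after discharge. Compliance is recorded at follow-up visits, and measures continue until all four videos are reported as watched or until the 1-year visit.
- **Eligibility Criteria.** Participants who wish to withdraw from the study are excluded, with no restriction to one group.
- **Statistical Analysis.** The section lists t tests at each follow-up, a mixed model for repeated measures, and separate intention-to-treat and per-protocol analyses under sensitivity analyses.

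The primary outcome is the Mini-MAC at 6 months (T2).

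**The concern.** Intention-to-treat means that each participant's outcome is analysed in the assigned group whether or not the programme was used. A rule that ends usable data at deviation from the programme describes a while-adherent analysis under another name.

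The rule is also lopsided. Controls receive routine information only, so no control can deviate from the intervention. A disengaged control keeps the T2 score. An equally disengaged intervention participant who misses the family medicine visit but still attends follow-up could lose it. The visit falls at the first follow-up after discharge, which should come before T2, although the text gives no date.

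Three things are at stake:

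- The primary comparison could be distorted by selective loss in one arm of a study that already relies on a historical control group.
- The sentence is offered as protection against attrition bias but could create it.
- If the intention-to-treat analysis also stops at deviation, it moves toward the per-protocol analysis, and the planned contrast between the two says little.

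**Working it through.** **Step 1. Two readings of departure, set against the other sections.**

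- *Departure from the intervention.* This fits the trigger, which names deviation as well as discontinuation; someone who deviates need not leave the study. It contradicts the intention-to-treat label in the same sentence, and for deviation it can apply to one arm only (Control Group).
- *Departure from the study.* This fits the stated aim of limiting attrition bias, and controls can leave too. It does not fit the word for deviation, and it conflicts with Eligibility Criteria: withdrawers are excluded there, but here their data up to leaving are included.

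Neither reading leaves the article consistent.

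**Step 2. The plan's own figure.** Sample Size Calculation gives an effect size of 0.25 and 252 per group. Power is not stated. With a two-sided 5% level and 80% power, n = 2 x (1.960 + 0.842)^2 / 0.25^2 = 251.2, rounded up to 252. Two-sided 90% power would need 337, one-sided 80% 198 and one-sided 90% 275, so two-sided 80% is inferred. Allowing for 16% dropout, 252 / 0.84 = 300. Both figures reproduce, and 0.25 SD serves as the yardstick below.

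**Step 3. Size of a one-sided cut (illustration).** Inputs from the article: 441 controls and 350 intervention participants (Results), 16% dropout (Sample Size Calculation), two-sided 5% (Statistical Analysis). Assumptions not in the article: the 16% applies equally to both arms; a further share q of the intervention arm is cut before T2; those cut would differ from the rest of their arm by g SD at T2; the comparison is unadjusted and uses available cases.

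- Controls at T2: 441 x 0.84 = 370.
- Intervention at T2: 350 x 0.84 x (1 - q) = 294 x (1 - q).
- Bias = q x g.
- SE = sqrt(1/n_control + 1/n_intervention), in SD units.
- Type I error = P(Z > 1.96 - bias/SE) + P(Z < -1.96 - bias/SE).

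| q | Intervention n | Power at 0.25 SD, ignoring bias | Bias, g = 0.25 | Type I error, g = 0.25 | Bias, g = 0.5 | Type I error, g = 0.5 |
|---|---|---|---|---|---|---|
| 0 | 294 | 89% | 0 | 5% | 0 | 5% |
| 10% | 265 | 87% | 0.025 | 6.1% | 0.05 | 9.5% |
| 20% | 235 | 85% | 0.05 | 9.2% | 0.10 | 22.4% |
| 40% | 176 | 78% | 0.10 | 19.4% | 0.20 | 59% |

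Worked case, q = 20% and g = 0.5: SE = sqrt(1/370 + 1/235) = 0.083; bias/SE = 0.10/0.083 = 1.20; P(Z > 0.76) + P(Z < -3.16) = about 0.22.

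At g = 0.25 the bias is 10%, 20% and 40% of the 0.25 planning effect. The loss of power is modest; bias is the main risk. Because the test is two-sided, its type I error is the same whichever way the gap points.

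**The case against.** The best defence is that the sentence is loose rather than wrong. It says which data are included, not that anything is thrown away. It follows a remark on retention in both groups and aims at attrition bias, so it may only mean that partial data from leavers are kept. The videos have no deadline, and participants who have not watched them appear to be seen up to 1 year. The separate per-protocol analysis makes more sense if the intention-to-treat analysis keeps non-adherers. The article also condenses a fuller protocol that is not shown.

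Much of this stands. A reader might infer that non-adherers' 6-month scores are definitely lost in the intervention arm. The text does not support that: it never says later data were discarded, and the follow-up described for non-watchers suggests that their T2 scores are probably obtainable.

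A reader might also infer that the loss would favour the programme, since Limitations says it "might be more appealing to participants who are actively seeking ways to adapt to life after cancer". That passage contrasts motivated with indifferent people; it does not say that the indifferent adjust worse, and some may skip the programme because they are coping well. The Mini-MAC total also adds helpless-hopeless and anxious-preoccupation items to positive-attitude items, so a disengaged patient could score higher or lower.

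The mixed model can use the T0 and T1 scores of people who are cut, which may reduce the bias, but only under missing at random. The t tests at each follow-up have no such help.

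What does not stand is the claim that nothing needs changing. The study-exit reading does not account for deviation and conflicts with Eligibility Criteria. Nor is this a detail left to another document: the article states a rule, and as stated it contradicts its own label.

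**Conclusion.** The point holds as a contradiction in the stated rule and a risk to the primary comparison, not as a demonstrated loss. Followed literally, Data Collection ties outcome data to adherence, calls the result intention-to-treat, and may remove 6-month scores from the intervention arm alone. On the other reading it conflicts with the exclusion of withdrawers. Either way the sections must be reconciled.

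The documents fix neither the direction nor the size of any bias. The illustration rests on assumed shares and gaps in an unadjusted available-case comparison: at a 0.25 SD gap, shares of 10-40% give 0.025-0.10 SD and a type I error of about 6-19%. The figure of about 22% needs a 20% share with a 0.5 SD gap and should not be read as an expected value.

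**What to change.** Replace the sentence in Data Collection with a rule to this effect: participants who discontinue or deviate from the intervention stay in follow-up; all T1-T3 scores obtained, before or after any deviation, are analysed in the assigned group; data end only at withdrawal of consent for follow-up, death or loss to follow-up, by the same rule in both groups.

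Define departure, or drop the word. Bring Eligibility Criteria, Delivery of the Intervention, Data Collection and Statistical Analysis into line with this rule, and keep adherence-based exclusion for the per-protocol analysis.

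The cost is a few sentences. The T1-T3 questionnaires are already scheduled for everyone, so no visits are added, and Results says that the analyses are to follow completion of the study, so the change was still open when the article appeared. The downside is that the estimated effect may be smaller because non-adherers count.
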